## Abstract

**Background:**

The REtirement in ACTion (REACT) study is a multi-centre, pragmatic, two-arm, parallel-group randomised controlled trial (RCT) with an internal pilot phase. It aims to test the effectiveness and cost-effectiveness of a community, group-based physical activity intervention for reducing, or reversing, the progression of functional limitations in older people who are at high risk of mobility-related disability.

**Methods/design:**

A sample of 768 sedentary, community-dwelling, older people aged 65 years and over with functional limitations, but who are still ambulatory (scores between 4 and 9 out of 12 in the Short Physical Performance Battery test (SPPB)) will be randomised to receive either the REACT intervention, delivered over a period of 12 months by trained facilitators, or a minimal control intervention. The REACT study incorporates comprehensive process and economic evaluation and a nested sub-study which will test the hypothesis that the REACT intervention will slow the rate of brain atrophy and of decline in cognitive function assessed using magnetic resonance imaging (MRI). Outcome data will be collected at baseline, 6, 12 and 24 months for the main study, with MRI sub-study data collected at baseline, 6 and 12 months.

The primary outcome analysis (SPPB score at 24 months) will be undertaken blinded to group allocation. Primary comparative analyses will be on an intention-to-treat (ITT) basis with due emphasis placed on confidence intervals.

**Discussion:**

REACT represents the first large-scale, pragmatic, community-based trial in the UK to target the non-disabled but high-risk segment of the older population with an intervention to reduce mobility-related disability. A programme that can successfully engage this population in sufficient activity to improve strength, aerobic capacity, coordination and balance would have a major impact on sustaining health and independence.

REACT is also the first study of its kind to conduct a full economic and comprehensive process evaluation alongside the RCT. If effective and cost-effective, the REACT intervention has strong potential to be implemented widely in the UK and elsewhere.

**Trial registration:**

ISRCTN, ID:ISRCTN45627165. Retrospectively registered on 13 June 2016.

Trial sponsor: University of Bath. Protocol Version 1.5.

**Electronic supplementary material:**

The online version of this article (10.1186/s13063-018-2603-x) contains supplementary material, which is available to authorized users.

## Background

During old age, there is a population-wide transition from independence and adequate physical function towards frailty and an increased demand for health and social care support services. In particular, the prevalence of mobility-related disability increases rapidly with age [1]. Frailty and associated co-morbidities compromise quality of life for older adults and contribute major societal costs; directly to people who live with frailty, to friends and family providing care and losing productivity, and to health and social care services [2, 3].

Physical inactivity is one of the strongest predictors of mobility-related disability in older adults [4]. A fit and active older person has a 36% lower risk of developing functional limitations and a 38% lower risk of hip fracture [5]. In the UK-based Opal Plus cohort, older people who undertook at least an average of 25 min of moderate to vigorous physical activity (MVPA) per day at baseline received fewer prescriptions and were less likely to be admitted to hospital in an emergency 4 to 5 years later [6].

Clinical trials have provided robust evidence that physical features of frailty, such as reduced muscular strength or endurance, can be reversed, or at least the progression of these frailty indicators can be slowed, by undertaking an appropriate exercise programme [7, 8]. Unfortunately, older adults are the least active segment of the UK population. Less than 30% of 65–74-year-olds report any moderate-intensity physical activity lasting at least 10 min in the previous 4 weeks [9]. Health Survey for England (HSE) data indicate that among people aged 65 years and above, 36% of women and 27% of men reported a need for help in the last month with one or more activities of daily living (ADLs) such as getting up and down stairs, dressing, getting around indoors, or shopping [10]. These people are in transition from independence to frailty and have a great deal to gain if loss of function can be reversed and independence maintained.

Sedentary behaviour and mobility limitations in older people are more prevalent in socio-economically deprived sectors of the population [11]. Ethnically diverse groups in the USA have a significantly greater risk of a range of physical and mental health problems compared to their White counterparts, and subsequently suffer higher rates of morbidity and premature mortality [12]. Self-reported data from the HSE indicate that older (55 + years) Bangladeshi, Pakistani and Indian adults in England are less likely to meet physical activity guidelines compared to their White European counterparts [10]. Thus, exercise interventions that can successfully engage and retain sedentary and ethnically diverse groups of older adults could contribute to the reduction of health inequalities.

Lifestyle Interventions and Independence for Elders **(**LIFE) is a landmark study in the field of physical activity promotion in older adults [8]. LIFE was a multi-centre randomised controlled trial comparing the effects of a physical activity programme with a successful ageing educational programme in more than 1600 functionally impaired older persons, over an average follow-up of 2.6 years. The intervention reduced the risk of developing major mobility disability (defined as the inability to complete a 400-m walk test within 15 min) [8] by 18% relative to the control group (Hazard Ratio (HR) 0.82: 95% confidence interval (CI), 0.69–0.98). It also reduced the risk of persistent mobility disability by 28% (major mobility disability at consecutive time points) (HR 0.72; 95% CI, 0.57–0.91). The intervention group maintained an increase of 40 min/week (95% CI, 29 to 52; *p* < .001) in objectively assessed lifestyle-intensity activity (≥ 760 counts/min compared with the control group at 24 months of follow-up). These estimates are likely to be conservative as the study utilised an active control group which received a substantial health education/lifestyle intervention including weekly workshops for 6 months and monthly sessions for a further 18 months.

Building on the success of the LIFE study in the USA, the REtirement in ACTion (REACT) study aims to test the effectiveness and cost-effectiveness of a community-based physical activity intervention for reducing, or reversing, the progression of functional limitations in older people who are at high risk of mobility-related disability.

## Methods

### Trial design

The study protocol is presented in accordance with the Standard Protocol Items: Recommendations for Interventional Trials (SPIRIT) guidelines (Additional files 1 and 2).

The REACT study is a multi-centre, pragmatic, two-arm, parallel-group randomised controlled trial with an internal pilot phase and that incorporates comprehensive process and economic evaluations. Following identification and recruitment, 768 participants who meet the study inclusion criteria will be randomised to receive either the REACT intervention, delivered over a period of 12 months by trained facilitators or a minimal control intervention. The pilot phase will assess the feasibility of recruitment methods (allowing for some refinement if needed) and confirm adequate retention rates in the intervention and the study, prior to progressing with the main trial. A nested sub-study, led by the Wellcome Centre for Integrative Neuroimaging, University of Oxford, employing magnetic resonance imaging (MRI), will test the hypothesis that the REACT intervention will slow the rate of brain atrophy and of decline in cognitive function. Outcome data will be collected at baseline, 6, 12 and 24 months for the main study, with MRI sub-study data collected at baseline, 6 and 12 months. The REACT study was reviewed and approved by the National Health Service (NHS) South East Coast-Surrey Research Ethics Committee (15/LO/2082). The study is registered as a current randomised controlled trial (ISRCTN45627165).

The REACT study will be conducted at three UK sites – Bath/Bristol, Devon and Birmingham – allowing recruitment of a socio-economically and ethnically diverse sample including participants from urban, rural and semi-rural locations.

### Study population

The eligibility criteria are intended to identify 768 sedentary, community-dwelling, older people aged 65 years and over with functional limitations (i.e. who are at risk of major mobility limitations), but who are still ambulatory, i.e. they can still walk. This will be measured using a battery of objective physical function tests (Short Physical Performance Battery (SPPB)) to assess balance, walking speed and the ability to change from a sitting to a standing position. This generates a physical function score from 0 to 12 older adults with scores of 4–9 (inclusive) out of 12 will be eligible to take part in REACT. This is based on data showing that older adults with SPPB scores of 9 or less have substantially higher risk of major mobility disability 3 years later (odds ratio (OR) = 8.3 (95% CI, 3.3 to 20.67) compared with those with a score of 12 [8, 13]. Inclusion and exclusion criteria are summarised in Table 1.

**Table 1 Tab1:** Eligibility criteria for participation in the REACT study and the magnetic resonance imaging (MRI) sub-study

Inclusion criteria	Aged 65 years or older and not in full-time employment Planning to reside in the target area (Bath/Bristol, Devon, Birmingham) for at least 24 months Score between 4 and 9 (inclusive) on the Short Physical Performance Battery (SPPB)
Exclusion criteria	Self-reported inability to walk across a room without a walker or the help of another person Existing major mobility limitation (defined as SPPB of 3 or less, or unable to complete the 4-m walk component of SPPB) Living in residential or nursing care Inability to attend the REACT physical activity sessions as scheduled A documented or patient-reported medical condition that would preclude participation, including: • Arthritis so severe it would prevent participation in physical activity • Parkinson’s disease or diagnosed dementia • Any terminal illness • Lung disease requiring use of orally administered corticosteroids or supplemental oxygen • Severe kidney disease requiring dialysis • Severe heart disease that would prevent participation in physical activity (e.g. chest pain when walking 100 or 200 yards or up a flight of stairs) • Implanted cardiac defibrillator • Cardiac arrest which required resuscitation • Severe uncontrolled psychiatric illness • Currently receiving radiation therapy or chemotherapy treatment for cancer • Awaiting knee or hip surgery • Major heart surgery (including valve replacement or bypass surgery) in the last 6 months • Unstable heart condition (e.g. uncontrolled arrhythmia, angina, heart failure or hypertension) • Spinal surgery in the last 6 months • Any other clinical condition that the person’s GP or clinician considers would make them unsuitable for participation in a physical activity rehabilitation programme to prevent decline of lower-limb functioning For the MRI sub-study: Contraindications for MRI scanning (assessed using CRIC Bristol Standard Operating Procedure for Screening Subjects for Safety to Scan (Ref MRI Local Rules and Procedures, 2011) History of neurological illness (e.g. stroke) Current treatment for a psychiatric illness Insufficient English to understand what participation entails and provide consent in English
Temporary exclusion criteria	Heart attack (or myocardial infarction), stroke, spinal surgery, hip fracture, hip or knee replacement within the previous 6 months Currently receiving physical therapy on legs or enrolled in another physical activity research or intervention study

### Recruitment

A range of recruitment strategies to identify suitable participants will be employed:

#### Primary care

General practitioner (GP) practices in the study catchment areas will be invited to participate through their local Clinical Research Network (CRN) and through existing networks. Where possible we will select practices to maximise diversity in terms of ethnicity, socio-economic status and (in Devon) rurality.

Practice staff will search the practices’ electronic patient databases for potentially eligible patients using the trial entry criteria (for criteria that are coded in the database). Lists generated from the searches will be further screened for suitability by a GP at each practice particularly to screen for items that are not included (or can only be partially covered) by the electronic searches. A Patient Approach Letter printed on the practice headed notepaper, a reply form and Participant Information Sheet (PIS) will be sent to suitable patients, with a reply paid envelope addressed to the research team at the local trial site. If the target recruitment rate is not achieved, practices will be asked to send out follow-up Participant Approach Letters to the same patients 14–21 days later. GPs and practice nurses may also offer the recruitment pack in surgery to patients who they consider would fit the REACT recruitment criteria.

#### Third-sector organisations

The principal investigators at each trial site will engage with third-sector and community-based organisations and authorities which work with adults over the age of 65 years. Professionals in these services will either approach potentially eligible service users and provide a brief summary of the study or invite the study researchers to give a presentation about the study, followed by provision of the Participant Approach Letter and PIS, if deemed appropriate. Publicity materials will be made available through libraries, supermarkets, post offices and GP surgeries.

#### Word-of-mouth and snowball sampling

To enhance recruitment, we will use word-of-mouth and snowball sampling techniques and employ the assistance of bi-lingual community champions. This approach will be particularly useful for engaging with ethnically diverse groups.

#### Local media

Recruitment will be supported by a low-cost public relations campaign targeting local newspapers, magazines, radio and community events.

Each REACT trial site will track recruitment methods to determine the most successful strategy for recruiting and for recruiting from diverse ethnic groups in particular.

### Eligibility screening

The eligibility of respondents will be assessed in a three-step sequential screening process:*Initial self-selection*: the Participant Approach Letters and PIS will make it clear that we wish to recruit people who are still able to complete but have some difficulty with daily activities such as walking, climbing stairs and getting out of a chair*Telephone-based screening*: after gaining verbal consent a preliminary telephone screen will check inclusion and exclusion criteria that can be assessed by telephone (e.g. self-reported inability to walk across a room), including a second check on medical exclusion criteria (e.g. recent heart surgery). Ability to attend intervention sessions will also be checked. Participants who do not meet the eligibility criteria will be thanked for their time and provided with an information pack including the Age UK/NHS guide to Health Ageing and sources of further advice and information*Face-to-face screening sessions*: potentially eligible participants will then be invited to a group-based assessment session where they will have an opportunity to ask questions about the study and be asked to give written informed consent. The SPPB Gait Speed Test will be conducted first, and those who fail to complete the 4-m walk, or do not meet the other SPPB inclusion criteria, will be thanked for their time and provided with an information pack (as above). Participants who meet the eligibility criteria will be invited to complete the remainder of the baseline assessments*MRI sub-study*: REACT participants who consent to discuss participation in the MRI sub-study will be screened for exclusion criteria using the CRIC Bristol SOP Screening Subjects for Safety to Scan [14]. This will be repeated immediately before the MRI scan

### Consent

Older adults who are willing to take part in REACT will be asked to provide written informed consent prior to commencement of the face-to-face screening sessions. The consent process will involve a brief recap of the PIS and an opportunity to ask questions prior to any of the face-to-face screening/baseline data collection processes commencing. Potential participants will be informed that they may, at any time, withdraw their consent to participate in the study without giving a reason, and without it affecting their relationship with their GP or the referring organisation and/or their future treatment and care.

### Randomisation/allocation

When 30 eligible participants have been recruited (enough to form one study group) they will be randomised to one of the two arms (physical activity (intervention) arm or social and education (control) arm using a secure, centralised, web-based randomisation website built by Peninsula Clinical Trials Unit (CTU). Randomisation will be performed using a minimisation algorithm to balance groups in terms of study site (Bath/Bristol, Birmingham, Exeter/Devon), age group, gender and initial functional ability (SPPB score). This algorithm has been built by the Peninsula CTU and uses the method proposed by Taves and extended by Pocock et al. [15, 16]. It maintains a stochastic element by computing probabilities proportional to the existing imbalance at the point of randomisation.

During the pilot phase, the randomisation will be 2:1 (intervention/control) in order to enable feasibility testing of intervention engagement and retention as early as possible. The main trial randomisation will be 1:1. Couples presenting together at the screening where both people are eligible and willing to be involved in the study will be randomised together to reduce contamination between study arms.

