### Statistical analysis

Primary outcome analysis will be undertaken blinded to group allocation. Primary comparative analyses will be on an intention-to-treat (ITT) basis with due emphasis placed on confidence intervals. Using appropriate descriptive statistics, we will assess any imbalance between the trial arms at baseline and describe the characteristics of participants. The comparison of primary interest is the difference between the intervention and the control arm on SPPB score at the 2-year follow-up. This will be presented as between-group differences in means, 95% CIs and *p* values. Covariates in the model will comprise of baseline SPPB scores, centre, age group and gender.

Depending on the extent of missing primary outcome data, the primary analysis will be repeated using the complete data set generated using multiple imputations. Sensitivity analyses will be conducted to investigate the potential effects of missing data and of any co-interventions on the conclusions.

Secondary outcome analysis will be undertaken using the same general approach as for the primary analysis, using the baseline, 6-month, 1-year and 2-year follow-up data. This will include linear or logistic regression models for continuous or binary outcomes as appropriate.

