#### Adjusted analysis

Using appropriate descriptive statistics, we will assess any imbalance between the trial arms at baseline and describe the characteristics of participants. As participants are randomised using the method of minimisation we are not expecting significant imbalance between groups. However, the minimisation variables (age, gender, SPPB) will be adjusted for in the statistical analysis.

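### Allocation moves from 2:1 in the internal pilot to 1:1 afterwards, but neither the stated primary model nor the minimisation includes recruitment phase, so arm is associated with recruitment period by design

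*Protocol article*

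**What the plan says.** All references are to the protocol article.

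- **Allocation.** Randomisation/allocation states: "During the pilot phase, the randomisation will be 2:1 (intervention/control" arms), followed by "The main trial randomisation will be 1:1". The same section says minimisation is used to "balance groups in terms of study site (Bath/Bristol, Birmingham, Exeter/Devon), age group, gender and initial functional ability (SPPB score"). Phase is not among these factors.
- **Status of the pilot.** Trial design describes a "parallel-group randomised controlled trial with an internal pilot phase". The sample size section gives a single total of 768.
- **Purpose of the pilot.** Trial design says: "The pilot phase will assess the feasibility of recruitment methods (allowing for some refinement if needed").
- **Primary model.** Statistical analysis states: "Covariates in the model will comprise of baseline SPPB scores, centre, age group and gender".
- **A second covariate statement.** Adjusted analysis says "the minimisation variables (age, gender, SPPB) will be adjusted for in the statistical analysis". Site is missing from that parenthesis, although it is a minimisation factor and centre is in the primary model.

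**The concern.** The probability of being allocated to the intervention is 2/3 in the pilot and 1/2 afterwards. Randomisation makes the arms comparable within each phase. It does not make them comparable across the two phases combined unless the analysis takes account of phase. In a pooled analysis without a phase term, any difference in outcome between pilot and main-trial participants that the other covariates do not explain is partly attributed to treatment.

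The article itself gives one reason why the phases might differ: recruitment methods may be refined after the pilot. Assessors and season are other possible sources. Adjusted analysis expects no important baseline imbalance because of minimisation. That expectation does not extend to phase, where the imbalance is planned and the algorithm does not address it.

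At stake is a shift in the estimated difference in 24-month SPPB, in a direction that cannot be known in advance, and some inflation of the type I error.

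**Working it through.** **Inputs from the article.** Total 768 (384 per arm), target difference 0.5 points, SD 2.0, two-sided 5% level, 85% power, loss of 12.5% per year for two years (25% if summed), allocation 2:1 then 1:1.

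**Inputs assumed.** Pilot size P is not stated; I take 60 to 180. The phase difference δ in 24-month SPPB that remains after adjustment is not stated; I show 0.5 and 1 point. I also assume equal loss in both arms and phases, the same treatment effect in both phases, and 1:1 allocation in the main phase without compensation for the pilot excess.

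**Step 1: reproduce the plan's figure.** Evaluable n per arm = 2 × (1.960 + 1.036)² × 2.0² / 0.5² ≈ 287.3, rounded up to 288. Then 288 / 0.75 = 384 per arm, 768 in total. The stated sample size is reproduced. The planning standard error is 2.0 × √(2/288) ≈ 0.167.

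**Step 2: arm sizes and pilot shares.** Intervention n = 2P/3 + (768 − P)/2. Control n = P/3 + (768 − P)/2. Pilot share is (2P/3)/intervention n and (P/3)/control n.

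| P | Intervention / control n | Pilot share, intervention | Pilot share, control | Gap (points) |
|---|---|---|---|---|
| 60 | 394 / 374 | 40/394 = 10.2% | 20/374 = 5.3% | 4.8 |
| 120 | 404 / 364 | 80/404 = 19.8% | 40/364 = 11.0% | 8.8 |
| 180 | 414 / 354 | 120/414 = 29.0% | 60/354 = 16.9% | 12.0 |

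**Step 3: bias without a phase term.** Bias ≈ gap × δ.

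| P | δ = 0.5 | δ = 1 |
|---|---|---|
| 60 | 0.024 | 0.048 |
| 120 | 0.044 | 0.088 |
| 180 | 0.060 | 0.120 |

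At δ = 0.5 the bias is 0.024/0.167 ≈ 0.14 to 0.060/0.167 ≈ 0.36 standard errors, and the type I error is about 5.2% to 6.5%. At δ = 1 the type I error is about 6.0% to 11.1%, and the largest bias is 0.120/0.5 = 24% of the target difference.

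**Step 4: sensitivity to rebalancing.** If the main phase brought the totals back to 384 each, the gap would be (2P/3 − P/3)/384 = P/1152, which is 5.2 points at P = 60 and 15.6 points at P = 180. The bias at δ = 0.5 would then be 0.026 to 0.078.

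**Step 5: price of the phase term.** With phase in the model, the information about the effect is the sum over phases of n_I × n_C / (n_I + n_C) / 2.0², using evaluable numbers (75% of those randomised).

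- P = 60: 30 × 15/45/4 + 265.5/2/4 = 2.50 + 33.19 = 35.69. The standard error is 0.167 and power 84.8%, against 85.1% without the term.
- P = 180: 90 × 45/135/4 + 220.5/2/4 = 7.50 + 27.56 = 35.06. The standard error is 0.169 and power 84.2%, against 84.9% without the term.

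The loss is 0.3 to 0.7 percentage points.

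**The case against.** The strongest reply is that the bias is conditional and probably small. It needs a phase difference in 24-month SPPB that survives adjustment for baseline SPPB, centre, age group and gender, in people who all entered with an SPPB of 4 to 9. Much drift in case mix would be absorbed by those covariates. The article reports no drift and allows refinement of recruitment methods only if needed. A residual difference of 1 point is twice the target effect and half the planning SD, so the upper end of the range is unlikely. All of this stands, and it limits the size of the point. It does not remove the association between arm and period, which the allocation rule creates.

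A second reply is that the SAP, which is not shown, may add phase. It may. But the article does not merely leave the model open: it says what the covariates will comprise, and phase is not among them. It is also true that no sentence says the phases will be pooled; that is inferred from the internal pilot and the single total.

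Three stronger readings are tempting but unsupported:

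- A reader might infer that the two covariate statements cause the confounding. They do not. The model under Statistical analysis already includes centre, and fitting it satisfies Adjusted analysis as well; the missing site is an editorial slip.
- A reader might count changes in programme delivery between phases as confounding. Such changes would make the treatment effect differ by phase, so the pooled result would average two effects. A phase main effect would not alter that.
- A reader might infer that 2:1 allocation undermines the sample size. Without a phase term, power is still 84.9% at P = 180.

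**Conclusion.** The point holds in a limited form. Arm and recruitment period are associated by design, and the stated model does not adjust for it. With a pilot of 60 to 180 and no rebalancing, the pilot share differs between arms by 4.8 to 12.0 percentage points, and the bias is 0.02 to 0.06 SPPB points for each 0.5 points of residual phase difference. That is well under half a standard error at a 0.5-point difference, so the bias is probably modest.

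The allocation ratios and the covariate list are plain in the text. The size rests on a pilot size and a residual phase difference that the article does not give. The documents do not show that the estimate will be biased, only that the stated model leaves it unprotected if the phases differ.

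**What to change.** Add recruitment phase (pilot 2:1 versus main 1:1) as a fixed effect in the primary and secondary models, and say so before the primary data are analysed. Phase is known from the date of randomisation, so no new data are needed. The cost is one degree of freedom and under 1 percentage point of power. Fitting randomisation batch instead would also cover phase, but with groups of 30 there would be about 768/30 ≈ 26 batches, so it is not an equally cheap substitute.

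State the pilot size, and whether pilot counts carry over into the minimisation for the main phase, so that the gap can be calculated rather than assumed.

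Separately, as an editorial correction, add site to the minimisation variables named under Adjusted analysis so that the sentence agrees with Randomisation/allocation and Statistical analysis.
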